#### Outcomes

Table 2 shows the primary and secondary endpoints, including the definition, functional form of the variable, and measurement approach. Figure 5 shows the schedule of enrollment, intervention, and assessment. The primary outcome is heart rate; we collect three measurements monthly from every participant during monthly home visits. In addition to the primary outcome, we are collecting data to assess the effects of cool roofs on (i) secondary environmental outcomes, including ambient temperature and humidity (measured using iButton sensors), and (ii) secondary health outcomes, such as blood pressure, body temperature, heat-related outcomes, blood glucose, sleep, cognition, mental health, health facility utilization, economic and productivity outcomes, mosquito count, life satisfaction, gender-based violence and food consumption. We randomly selected 152 participants [intervention, *n* = 76 (38 women, 38 men) versus control, *n* = 76 (38 women, 38 men)] to receive a smartwatch that continuously monitors heart rate, sleep, and activity. Between August 2021 and July 2022, our participants used the Withings Pulse HR smartwatch for data collection. In July 2022, owing to the fragility of the Withings Pulse HR, we replaced these devices with the Garmin Vivosmart 5 smartwatch. Several Withings Pulse HR smartwatches were breaking with participant use in the field, necessitating this replacement.

**Table 2 Tab2:** Primary and secondary endpoints of the cRCT

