**Secondary endpoints**	
**Air temperature**	Definition: Ambient air temperature (in °C) Functional form: Continuous Measurement: DS1923 iButton Hygrochron heat and humidity measurement device
**Relative humidity**	Definition: Ratio of the amount of water vapor present in the air to the greatest amount possible at the same temperature (in %) Functional form: Continuous Measurement: DS1923 iButton Hygrochron heat and humidity measurement device
**Heat index**	Definition: Index that combines air temperature and relative humidity (using the formulae endorsed by the US National Oceanic and Atmospheric Administration (NOAA)) Functional form: Continuous Measurement: DS1923 iButton Hygrochron heat and humidity measurement device
**Indoor thermal comfort**	Definition: Current heat experience measured using heat strain score index. A score of < 13.5 indicates no or low heat strain, between 13.6–18 indicates potential for heat-induced illness, and > 18 indicates the onset of heat-induced illness Functional form: Categorical Measurement: Heat strain score index scale comprising 18 questions answered by individuals at the time of interview
**Systolic blood pressure**	Definition: Systolic blood pressure in mmHg Functional form: Continuous Measurement: Omron portable automated sphygmomanometers
**Diastolic blood pressure**	Definition: Diastolic blood pressure in mmHg Functional form: Continuous Measurement: Omron portable automated sphygmomanometers
**Body temperature**	Definition: Body temperature Functional form: Continuous Measurement: Inner ear thermometer
**Dehydration**	Definition: Loss of fluid greater than intake amount resulting in the body being unable to carry out its normal functions Functional form: Categorical Measurement: Urine hydration chart and question answered by individual
**Blood glucose (HbA1c)**	Definition: Average blood glucose measured over 3 months Functional form: Continuous Measurement: HemoCue® HbA1c 501 System to capture estimated average glucose (g/L)
**Sleep**	Definition: Number of hours slept and number of times the individual woke up Functional form: Count Measurement: Recall question answered by individual and smartwatch (in a subset of the cRCT population)
**Cognition**	Definition: The mental processes involved in gaining knowledge and comprehension Functional form: Continuous Measurement: Oxford Cognitive Screen (OCS)-Plus (assessing memory, language, visual-spatial ability, and executive functioning domains)

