#### Analysis of smartwatch data

Raw indoor and outdoor temperature and relative humidity data, collected in 15-min intervals, will be averaged at the hourly level. We will categorize environmental data as anomalies when measurements are two standard deviations beyond the corresponding monthly average values based on roof type (mud brick or tin roof).

We will analyze data from smartwatches on heart rate and sleep. First, for heart rate data, we will exclude duplicate heart rate measurements or those that exceed the age-predicted maximum heart rate as implausible values. We will round and aggregate remaining heart rate measurements to the nearest 1-h interval to align with summarized indoor and outdoor temperature and relative humidity data. To distinguish daytime and nighttime heart rates, we will use median sleep onset and offset to define nighttime from 22:00 to 06:00 h. Measurements will be analyzed if they reach the threshold of at least 1 h during the same day or night, with a minimum of one measurement every 15 min. The 15-min threshold was selected based on previous research [53]. Second, for sleep data, we will calculate sleep duration based on onset and offset time to eliminate errors and minimize outliers. Only overnight sleep periods, where nighttime sleep is defined as having a sleep onset of ≥ 17:00 and a sleep offset of ≤ 13:00, with a 2-h adjustment made to account for earlier bedtimes of the study population, will be included in the analysis. If a participant has multiple sleep observations in a single night, we will aggregate these into one sleep observation by adding the sleep duration values and the duration between the first offset and last onset to the wake time after sleep onset. We will exclude data where multiple sleep observations overlap for a participant. Furthermore, sleep detections with a time difference of fewer than 3 h between sleep onset and sleep offset will be excluded, in line with the manufacturer’s declaration that such detections represent invalid measurements.

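### On nights with three or more sleep observations, the smartwatch merging rule counts every middle sleep period as both sleep and wake time.

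*Protocol article*

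**What the plan says.** The section Analysis of smartwatch data sets the handling of multiple records: "If a participant has multiple sleep observations in a single night, we will aggregate these into one sleep observation". The merge is done by "adding the sleep duration values and the duration between the first offset and last onset to the wake time after sleep onset". I read this in the only sensible way: durations are summed to give sleep, and the stated interval goes to wake time. The rule has no upper limit on the number of observations and subtracts nothing from the interval.

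Three other rules in the same section bear on it:

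- Overnight window: "nighttime sleep is defined as having a sleep onset of ≥ 17:00 and a sleep offset of ≤ 13:00".
- Overlap: "We will exclude data where multiple sleep observations overlap for a participant".
- Minimum length: "sleep detections with a time difference of fewer than 3 h between sleep onset and sleep offset will be excluded", because the manufacturer treats such records as invalid.

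The section does not say whether the overlap and minimum-length exclusions run before or after the merge. In the text they follow it.

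Table 2 defines the sleep endpoint as "Number of hours slept and number of times the individual woke up". Wake time after sleep onset is not named there. The section Outcomes says that 152 participants (76 per arm) were selected "to receive a smartwatch that continuously monitors heart rate, sleep, and activity".

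**The concern.** A night with three sleep periods has two gaps. The interval from the first offset to the last onset spans both gaps and also the sleep between them. Since the summed durations already include that sleep, the same hours enter the data as sleep and as wake, and the total exceeds the time that elapsed.

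At stake is any result that uses smartwatch wake time. The section goes on to model watch-based sleep outcomes for intervention effects. If wake time is among them, an affected night enters with an error that can be larger than the true value. The error also grows with the number of periods, so wake time would mislead most on the nights with most interruptions.

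**Working it through.** **Inputs.** The merging rule, the overlap exclusion, the 3 h minimum and the window come from Analysis of smartwatch data. The window is 24 - 17 + 13 = 20 h long. The document gives no example nights, so the clock times and the 0.5 h gaps below are my assumptions. No figure in the plan depends on this rule, so there is none to reproduce.

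**Formula.** Take k ordered, non-overlapping periods with onset a_i and offset b_i.

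- Rule as written: W_rule = a_k - b_1
- Wake between periods: W_gap = sum over i = 1 to k-1 of (a_{i+1} - b_i)
- Difference: W_rule - W_gap = sum over i = 2 to k-1 of (b_i - a_i), the total length of the middle periods

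The difference is zero for k = 2 and positive for k of 3 or more.

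**Worked night.** 20:00-23:00, 23:30-02:30, 03:00-06:00. Every period lasts 3 h, so the night survives the minimum whichever order applies.

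- Sleep: 3 + 3 + 3 = 9 h
- Rule: 23:00 to 03:00 = 4.0 h
- Gaps: 0.5 + 0.5 = 1.0 h
- Excess: 4.0 - 1.0 = 3.0 h, the length of 23:30-02:30
- Rule total: 9 + 4 = 13 h in a span of 10 h (20:00 to 06:00)
- Gap total: 9 + 1 = 10 h, which matches the span

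**Other patterns, all with 0.5 h gaps (hours).**

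| Periods | Sleep | Wake by rule | Wake by gaps | Excess | Sleep + rule wake | Span |
|---|---|---|---|---|---|---|
| 2 x 4 | 8 | 0.5 | 0.5 | 0 | 8.5 | 8.5 |
| 3 x 3 | 9 | 4.0 | 1.0 | 3.0 | 13.0 | 10.0 |
| 4 x 3 | 12 | 7.5 | 1.5 | 6.0 | 19.5 | 13.5 |
| 3 x 2.5 | 7.5 | 3.5 | 1.0 | 2.5 | 11.0 | 8.5 |
| 4 x 2 | 8 | 5.5 | 1.5 | 4.0 | 13.5 | 9.5 |

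**Effect of the exclusion order.** If the 3 h minimum acts on each detection before merging, the last two rows lose all their periods. An affected night then needs at least 3 x 3 = 9 h of recorded sleep, and its excess is at least 3 h. That fits the 20 h window but is longer than the 8 h from 22:00 to 06:00 that the section derives from median sleep times. If the minimum acts after merging, the last two rows stay in, with excesses of 2.5 h and 4.0 h.

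**Between arms.** The mean error per night is the share of affected nights times their mean middle-period length. If that length is 3 h in both arms, each percentage point of difference in the share shifts the arm contrast by 0.01 x 3 h = 0.03 h, or 1.8 min. With equal shares and equal lengths the contrast does not shift, but the level of wake time is too high and noise is added.

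**The case against.** The strongest reply is about reach. The rule is exact for two periods. If the 3 h minimum applies to each detection, as the word for device records and the manufacturer's rationale suggest, nights broken into short bouts drop out and only unusually long nights are affected. Hours slept are summed correctly, the count of awakenings does not use this interval, and wake time is not in the Table 2 definition. The primary outcome is untouched. All of this stands and keeps the point small.

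It might also be said that derivation code belongs in a fuller document. That carries less weight, because the article does not leave the rule out: it states it, for any number of observations, and in a form that fails beyond two.

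A reader might infer something stronger: that the rule inflates wake time on just the fragmented nights that heat produces, and so exaggerates the benefit of cool roofs. The document does not support this. It gives no frequency of nights with three or more periods, does not link them to heat, and does not say that they differ by arm. Two-period nights are fragmented as well and are handled correctly. Nor is there a basis for saying that a sleep efficiency measure is wrong, since the document plans none.

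**Conclusion.** The point holds in a narrow form. Read literally, the rule counts every middle sleep period as both sleep and wake when a night has three or more observations, and the inflation equals the total length of those periods. This is algebra and needs only that the periods are ordered and do not overlap.

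The size per affected night is 3.0 h in the three-period example. It is at least 3 h per affected night if short detections are removed first. The number of affected nights is unknown, and it depends on an exclusion order that the document does not state. The effect is confined to smartwatch wake time in 152 participants. A distorted arm comparison remains conditional on an imbalance between arms that nothing in the document demonstrates. This is a small error in a stated derivation rule, worth correcting because the correction is nearly free.

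**What to change.** Define the added wake time as the sum of the gaps between consecutive sleep periods, each gap being an onset minus the preceding offset. Two-period nights keep their present values.

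State that the overlap and 3 h exclusions are applied to single detections before merging. This agrees with the stated reason that short detections are invalid; applying the minimum to the merged night would readmit them. Under this order, the time of a removed detection lying between two valid ones falls into a gap and counts as wake, so the text should say whether that is intended.

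A useful code check is that the onset-to-offset lengths plus the added gaps equal last offset minus first onset. Any wake recorded within a period must be left out of this check, or correct nights could fail it.

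The cost is one sentence and about one line of code. Trial status reports that data collection has ended, but the change only re-derives a variable from onset and offset times, provided these were kept for each detection.

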### Statistical analysis

#### Analysis of monthly home visit data

The analysis for our primary outcome, heart rate, will be performed on the principle of intention-to-treat (ITT). We will use generalized linear mixed models (GLMM) to analyze the causal effect of cool roofs on our primary and secondary endpoints. In addition to the base-case estimations, without covariate controls, we will also estimate the intervention effect of cool roofs by adjusting for covariates to boost statistical efficiency. We will adjust for clustering of standard errors at the household level.

To estimate the intervention effect of cool roofs on heart rate, we will report the effect estimates comparing intervention and control arms based on the hypothesis that effects will be greatest during the hottest month of the year (April). We will additionally report effect estimates at monthly intervals of data collection, except for HbA1c (which is measured in two time points), because we hypothesize the intervention effect will vary based on outdoor weather conditions during the trial period; therefore, we will include an interaction term between the intervention and the month of trial. We will perform additional sub-analysis by selected variables where relevant (i.e., by season, gender, age group, time of the day (day/night), and roof type). We will explore the use of different imputation methods for missing values in the covariates. We will conduct sensitivity analysis, including repeating analyses accounting for individuals lost to follow-up. All data analyses will be performed using R software.

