We will evaluate the intervention effects of temperature exposure on heart rate and sleep outcomes using generalized additive mixed models, with individuals nested within households as random terms. Natural cubic splines will be used to evaluate non-linear effects. In cases where non-linear effects are not detected, linear terms will be substituted in the final models. We will present effect estimates of daily exposure averages on daytime versus overnight periods when individuals are most likely present in their homes. Furthermore, we will present intervention effects during the hottest month (April), monthly aggregates, and an overall aggregate for the entire study period. Where relevant, models with continuous daily or intraday time series data will include the day of the year and month indicators to account for time trends and seasonality, respectively. We will present supplementary models with an interaction term between the intervention group and roof type to assess variations resulting from the thermal characteristics of household vernacular architecture.

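### The smartwatch models as described name nothing for serial correlation or differing temperature response within persons, so their temperature-effect and linearity tests can be too liberal

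*Protocol article*

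**What the plan says.** All references are to the Protocol article.

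- **Model.** The section Analysis of smartwatch data will study temperature exposure in relation to heart rate and sleep "using generalized additive mixed models, with individuals nested within households as random terms".
- **Shape.** Natural cubic splines are fitted first. The rule for dropping them is data-driven: "In cases where non-linear effects are not detected, linear terms will be substituted in the final models".
- **Time terms.** Where relevant, "models with continuous daily or intraday time series data will include the day of the year and month indicators".
- **Resolution.** Heart rate is prepared hourly: the plan is to "round and aggregate remaining heart rate measurements to the nearest 1-h interval". For reporting, "We will present effect estimates of daily exposure averages on daytime versus overnight periods".
- **Sample.** Under Outcomes: "We randomly selected 152 participants", 76 per arm. Watches were used from August 2021 and data collection ended on June 30, 2023 (Trial status), so a series can span up to 23 months.
- **Standard errors.** Under Analysis of monthly home visit data: "We will adjust for clustering of standard errors at the household level". The smartwatch section has no matching sentence.

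**The concern.** A random intercept for a person, and one for the household, absorbs a constant offset. Month and day-of-year terms absorb the calendar pattern common to everyone. Neither deals with two other features of dense wearable data. One is that a person's heart rate drifts, so neighbouring hours or days resemble each other beyond the constant offset. The other is that people differ in how they respond to temperature. Temperature is itself autocorrelated and is shared within a home, so it lines up with both features.

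With model-based errors, the standard error of the temperature effect is then too small. The test behind the spline-or-linear rule has the same fault, so apparent curvature may be kept when it is noise. At stake are temperature-response findings with intervals that are too narrow, from the analysis that uses the trial's densest data.

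**Working it through.** **Plan's own figure.** There is none to reproduce. The documents give no autocorrelation, error rate or sample size calculation for these models.

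**Inputs**
- From the documents: 152 wearers; the random terms, calendar terms and spline rule above. The 5% level is stated under Power calculations for heart rate only; I apply it two-sided to all tests here.
- Assumed: lag-1 autocorrelation of temperature after calendar terms (a), lag-1 autocorrelation of the residual (b), share of days worn, spread of personal temperature slopes, and two wearers per household (76 homes).

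**Step 1. Analytic size for a gap-free AR(1) exposure and AR(1) residual.**
Variance inflation V = (1 + ab)/(1 − ab). Actual error rate = 2 × [1 − Φ(1.96/√V)].

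| a | b | V | √V | Error rate |
|---|---|---|---|---|
| 0.7 | 0.1 | 1.07/0.93 = 1.15 | 1.07 | 6.8% |
| 0.7 | 0.5 | 1.35/0.65 = 2.08 | 1.44 | 17.4% |
| 0.9 | 0.8 | 1.72/0.28 = 6.1 | 2.5 | 43% |
| 0.95 | 0.9 | 1.855/0.145 = 12.8 | 3.6 | 58% |

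The last two rows resemble hourly series. An error rate of 10% needs V = 1.42, that is ab = 0.42/2.42 ≈ 0.17. An error rate of 50% needs V = 8.44, that is ab = 7.44/9.44 ≈ 0.79.

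**Step 2. Daily simulation, autocorrelation only.** 365 days, month indicators plus day of year, person effects removed, 250 runs per setting (Monte Carlo error about 1.4 points at 5%). Rejection of a true null, slope test / linearity test:

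| a | b | All days worn | Half of days worn |
|---|---|---|---|
| 0.7 | 0.2 | 7.2% / 7.2% | 5.2% / 5.6% |
| 0.7 | 0.4 | 10.4% / 14.4% | 9.6% / 9.6% |
| 0.7 | 0.6 | 18.0% / 15.6% | 11.2% / 8.0% |
| 0.9 | 0.8 | 32.8% / 52.0% | 21.2% / 36.8% |

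**Step 3. Adding slope variation.** About 700 days, half worn, a = 0.7, 250 runs per setting. With b = 0.5 alone, the slope test rejects 10% and the linearity test 13%. Adding a between-person slope SD of 0.2 bpm per °C gives 38% and 34%. In a further set of 200 runs, a slope SD of 0.1 with no residual autocorrelation at all gave 12% for the slope.

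**Step 4. Arm contrasts.** In 2000 runs at b = 0, 0.4 and 0.8, the overall arm contrast rejects 4.6%, 5.5% and 4.6%. A test of whether the arm effect in April differs from other months rejects 4.0%, 19.0% and 48.1%. The simple April difference in level between arms stays at 5% to 8% in the autocorrelated scenarios of Step 3.

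**Step 5. Effect of household-clustered standard errors on the same fits.** The slope test rejects 3.6% to 7.6% in Step 2 and about 5% to 6% in Step 3. The linearity test falls to about 3% to 10%. The 10% arises when b = 0.5, slope SD 0.2 and person-by-month drift (SD 2 bpm) occur together; the model-based rate there is 35%. An AR(1) residual was not simulated.

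**The case against.** The strongest reply is that this is silence, not error. The text says random terms, not random intercepts only. It does not say readings are treated as independent, and a condensed article may leave the residual structure to an analysis plan that is not shown. A reader might infer that the plan has committed itself to independence within a person; the wording does not support that. What stands is narrower. The article does specify a dependence structure, calendar terms and a data-driven shape rule for these series, in a section detailed enough to give wear thresholds and sleep-overlap rules. Followed as written, that specification leaves serial correlation and slope differences unhandled.

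Second, the household-clustering sentence follows one covering primary and secondary endpoints, and watch heart rate and sleep are listed measurements of those endpoints. It may have been meant to reach the watches. But it stands under the home-visit heading and belongs to the GLMM description, whereas the smartwatch GAMMs are specified separately. Its reach is unclear.

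Third, the size rests on assumptions. A reader might infer a fixed multiple of 5%; the documents give no autocorrelation, wear share or slope spread to support one. The 43% and 58% figures need strong, gap-free, hourly-like autocorrelation, while Methods: monitoring reports watches being removed, particularly at night, and the reported estimates use daily exposure averages. No test or level is stated for detecting non-linearity, and two wearers per home is also an assumption. All of this stands, so only a conditional range can be given.

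**Conclusion.** The point holds in conditional form. With random intercepts and model-based errors, the described smartwatch models are anti-conservative for within-person temperature effects and for the spline-or-linear decision. The range over the assumptions tried, roughly 1 to 11 times nominal, contains both a negligible and a serious problem. Wear gaps and weak autocorrelation shrink it, but modest slope variation between people can restore some of it.

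A reader might infer that the trial's treatment effect is in doubt. It is not: the overall randomised contrast keeps its size, and the primary heart-rate analysis uses monthly sphygmomanometer readings with household clustering already stated. Tests that the arm effect changes from month to month could be inflated if run on watch data. An arm-by-temperature test is not named in the section, so nothing here rests on it. The point should be addressed, but it concerns temperature-response results in about 12% of participants.

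**What to change.** In Analysis of smartwatch data, state that the GAMMs use household-clustered (robust) standard errors, matching the home-visit analysis. Add a person-level AR(1) residual and a random temperature slope per person where the model converges. Base the choice between spline and linear term on that corrected variance. If clustering was always intended for the watch data, one sentence saying so removes the ambiguity.

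No new data are needed. The cost is a short addition to the plan, longer model runs in R, wider confidence intervals for temperature effects and probably fewer non-linear terms retained. Clustering alone may leave the linearity test somewhat liberal in the hardest scenario, which is a reason to add the AR(1) and slope terms where they can be fitted.

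### Both time terms named for the smartwatch models repeat each year, so they cannot separate year 1 from year 2 or adjust for the July 2022 watch change; pooled temperature-exposure estimates may be biased

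*Protocol article*

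**What the plan says.** The protocol article, under Analysis of smartwatch data, states the aim of these models: "We will evaluate the intervention effects of temperature exposure on heart rate and sleep outcomes using generalized additive mixed models". The random terms are specified "with individuals nested within households as random terms". Results are to be shown for the hottest month, by month, and as "an overall aggregate for the entire study period".

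The time terms are introduced with a qualifier, "Where relevant, models with continuous daily or intraday time series data", and are then fixed: these models "will include the day of the year and month indicators to account for time trends and seasonality, respectively". Day of the year is therefore the trend term and the month indicators are the season term.

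Under Outcomes, the article reports a change of instrument partway through: "Between August 2021 and July 2022, our participants used the Withings Pulse HR smartwatch for data collection", and then "In July 2022, owing to the fragility of the Withings Pulse HR, we replaced these devices with the Garmin Vivosmart 5 smartwatch". Trial status gives 30 June 2023 as the end of data collection.

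For the monthly home-visit data, the section on those analyses uses month of trial, which does not repeat, in an interaction with the intervention.

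**The concern.** A trend term has to tell an earlier date from a later one. Day of the year gives 1 March 2022 and 1 March 2023 the same value, and so does calendar month. The term assigned to trend is therefore a second seasonal term, and nothing named in the model distinguishes the first year of watch data from the second.

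This matters here because the change of watch falls almost exactly between those two years. A systematic reading difference between the two watches would appear as a step between years within each wearer. A constant random intercept per person cannot absorb a change within that person. A model that relates heart rate or sleep to temperature could then attribute part of the step to temperature, if same-season temperatures also differed between the years. Even without such a difference, the unmodelled step adds scatter to the temperature estimate. Randomisation does not help with this estimate, because it compares days rather than arms.

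**Working it through.** The plan states no figure for this point, so there is none to reproduce. Two questions were checked: how much of the watch change the named terms can absorb, and what an unabsorbed change could do to a temperature slope.

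**Inputs from the article**
- First watch from August 2021 and replacement in July 2022 (Outcomes).
- Data collection ended 30 June 2023 (Trial status).
- Time terms: day of the year and month indicators (Analysis of smartwatch data).

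**Assumptions, not in the article**
- Readings start on 1 August 2021. The switch falls on 1, 15 or 31 July 2022.
- True slope 0.30 beats/min per °C.
- Watch offset δ of 2 or 5 beats/min.
- Same-season temperature difference d between years of up to ±1 °C.
- Day-to-day temperature SD σ of 2 °C, shared by all homes.

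**Step 1: days covered.** 1 August 2021 to 31 July 2022 is 365 days, and 1 August 2022 to 30 June 2023 is 334 days. 365 + 334 = 699. With a switch on 15 July 2022, 351 of 699 days (p = 0.50) come from the second watch.

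**Step 2: what the terms absorb.** R² from linear regression over the 699 dates:

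| Outcome | Predictors | R² |
|---|---|---|
| Day of year | Calendar month | 0.993 |
| Watch change, 15 July | Day of year + month | 0.002 |
| Watch change, 1 July / 31 July | Day of year + month | 0.042 / 0.037 |
| Linear trend | Day of year + month | 0.218 |
| Watch change, 1 / 15 / 31 July | Running date + month | 0.998 / 0.957 / 0.993 |

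A spline in day of year raises the 15 July figure only to 0.014.

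**Step 3: effect on the temperature slope.** With the watch change left out and p near 0.5, the approximate shift in the slope is

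p(1−p) × δ × d / (σ² + p(1−p) × d²).

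- δ = 2, d = 1, σ = 2: 0.25 × 2 × 1 / (4 + 0.25) = 0.12. The slope becomes about 0.42, or about 0.18 when d = −1.
- δ = 5, d = 1: 1.25 / 4.25 = 0.29. The slope becomes about 0.59, or about 0.01 when d = −1.
- δ = 2, d = 0.25: 0.125 / 4.016 = 0.03.

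Simulation with autocorrelated temperature agrees: about 0.17 to 0.42 for a 2 beats/min offset, and about 0.00 to 0.58 for 5 beats/min. With watch model and running date added, the mean estimate is 0.30 in every setting.

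**Step 4: no year difference.** With d = 0 the mean bias is small, but chance differences between the years scatter the estimate. At a 2 beats/min offset the SD is about 0.05 under the planned terms and 0.01 under the amended ones. At 5 beats/min the planned-term SD is about 0.12.

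**Step 5: homes that vary independently.** Adding independent home-level variation of SD 1 to 2 °C to Step 3 (δ = 2, d = 1) gives 0.5 / 5.25 = 0.10 to 0.5 / 8.25 = 0.06. The slope is then about 0.40 to 0.36 rather than 0.42.

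**Step 6: arm contrast.** If both arms switch together and stay equally, the bias is zero. With assumed retention after the switch of 90% versus 80% and a 5 beats/min offset, the crude arm difference moves by 5 × (0.9/1.9 − 0.8/1.8) = 0.15. With 90% versus 70%, it moves by 5 × (0.9/1.9 − 0.7/1.7) = 0.31.

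**The case against.** **Bias is not shown.** It needs both a reading offset between the watches and a same-season temperature difference between the years, and the article gives neither. This stands. A reader might infer that the temperature effect is biased as a matter of fact, but the article supports only a risk of unknown size and sign.

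**The illustration is at the demanding end.** It uses a uniform 1 °C year difference and one temperature series for all wearers, whereas the trial logs temperature in each home. This also stands. The shift shrinks under Step 5, and at a 0.25 °C year difference it is about 0.03.

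**The arm comparison is safe.** This largely stands. Smartwatch wearers were randomly selected, 76 per arm. The article reports watch breakage, retention difficulties and removal of watches, but no difference by arm. A reader might infer from these problems that the arm effect is compromised, but the article does not support that. The sizes in Step 6 rest on assumed imbalance and are for a crude difference, before the person-level random terms.

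**A device term may sit in an analysis plan that is not shown.** This is fair, and the absence of such a term is not the point. The point is that a term named for trend cannot do that job.

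**The terms apply only where relevant, and the month indicators might mean month of trial.** The qualifier concerns when the terms are used, not what they are. Month of trial would absorb 96% to 100% of the switch, but the sentence assigns the month indicators to seasonality, so calendar month is the natural reading.

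**Some trend is absorbed.** This is correct: 22% of a linear trend, the within-year part. The step between years is not absorbed.

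**Conclusion.** The specification is wrong as written. Over about 23 months of watch data, the term assigned to trend is cyclical, and the two named terms leave 96% or more of the watch change unadjusted. That finding depends only on calendar dates and holds for any switch date tried in July 2022.

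The consequence is conditional. If the watches read differently, temperature-exposure estimates for heart rate and sleep pooled over both years lose precision. They are also biased if same-season temperatures differed between the years. The range of about 0.17 to 0.42 around an assumed 0.30 beats/min per °C is an illustration, not an estimate for this trial.

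The scope is limited. It concerns the 152 smartwatch wearers among 1200 participants. The primary heart-rate analysis uses monthly sphygmomanometer readings and is unaffected. The randomised smartwatch comparison is also unaffected so long as the arms changed watches together and contribute similar shares of data from each watch. The change should be made, but nothing here undermines the main result.

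**What to change.** In the smartwatch heart-rate and sleep models:
1. Replace day of the year as the trend term with running calendar date (linear or spline), or with month of trial as in the home-visit analysis.
2. Keep calendar month for seasonality.
3. Add an indicator for watch model.
4. Report results separately by device period as a sensitivity check, and tabulate by arm the share of data from each watch, so that the condition protecting the arm comparison can be verified.

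This needs no new data and only a few model terms. Given month, running date and watch model are nearly collinear (R² 0.96 to 1.00), so their separate coefficients should not be interpreted as a device effect and a trend effect. That does not harm the temperature estimate: in simulation the amended model recovered the assumed slope with less scatter than the planned one.
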